### Secondary outcomes

We will include additional tests following the ROMA consensus statement [30] for aphasia treatment research: General Health Questionnaire (GHQ)-12, Stroke Aphasia Quality of Life Scale (SAQOL-39), and the Western Aphasia Battery Revised (WAB-R). In addition, we will include the Stroke Aphasic Depression Questionnaire (SADQ10) to detect depressed mood and we will analyze the number of dropouts. An amendment to the protocol (protocol version 2.0; dated 7 October 2020), which was approved by the ethics committee prior the start of the recruitment, included a substudy to evaluate idiosyncratic and generalization effects with an ancillary multiple-baseline design [31]. We will randomly select 10 participants from the larger group of participants. The single-subject analysis will be comprised of three phases: baseline, treatment, and post-test. The assessor will be blind to the phase status of the participants. Generalization will be assessed by presenting 10-trial blocks of untrained words, untrained words in context, and trained words in context. In the untrained-word trials, the examiner will present a word that had not been used during treatment and will ask the participant to repeat it (e.g., please, repeat “lights”). In the untrained-word-in-context trials, the examiner will present a fill-in-the-blank phrase for target words that had not been used during treatment. Lastly, in the trained-word-in-context trials, the examiner will present a fill-in-the-blank phrase for target words previously used during treatment. We will establish the effect of the intervention for the three types of words (i.e., untrained, untrained in context, trained in context) using the Hedges-Pustejovsky-Shadish model [32]. Effect sizes will be calculated for all two-term comparisons (i.e., baseline vs. treatment, baseline vs. post-test, and treatment vs. post-test). To obtain inter-observer agreement, we will record the audio of 20% of the baseline, treatment, and post-test sessions. An agreement is defined as two independent observers recording the same trial outcome (e.g., correct, incorrect, no response). Interobserver agreement will be computed as the number of trials with agreement divided by the total number of trials multiplied by 100.

### Data management and monitoring body

Data will be prospectively included in a study-specific database developed with REDcap software (REDCap 8.7.4 - 2021 Vanderbilt University). All data management will follow the principles of the European regulations for biomedical research ensuring confidentiality. In compliance with European regulations/International Conference of Harmonization Good Clinical Practice Guidelines, the investigator and the institution are required to permit direct access to authorized representatives of the Ethics Committee to review the subject’s original medical records for verification of study-related procedures and data. Monitoring will be conducted by dedicated personnel at the Clinical Trial Unit at La Paz University Hospital.

### Sample size estimates

A formal sample size calculation is not possible given that this is a pilot study on a new therapy. However, based on a previous feasibility clinical trial on a different SLT in patients with post-stroke aphasia developed by our group [33], we estimated that we would need a sample size of 27 patients in each arm for an 80% power and a 0.050 two-sided significance level to detect a significant effect on the CAL evaluation [28]. Following the CONSORT guidelines for randomized pilot and feasibility trials, [26] upon the completion of this pilot trial we will estimate the sample size calculation for a definitive trial to evaluate the efficacy of this new therapy.

To achieve adequate participant enrolment to reach the target sample size, the following strategies will be implemented: stroke patients admitted to the Stroke Unit of La Paz University Hospital with post-stroke aphasia will be followed up at least 3 months after their stroke and, after the completion of the standard SLT, will be invited to participate in this study. Moreover, we will retrospectively review the clinical charts of patients discharged from the Speech Therapy Unit at La Paz University Hospital during the year before the start of the study and invite them also to participate. Finally, we will provide leaflets with the relevant study information to stroke patients’ associations. The cross-over design allows this experimental therapy to be offered to all the patients who participate in the trial, therefore reducing the possible rate of refusal to be enrolled in the control group. To ensure the follow-up, we will adapt the schedules of the dubbing sessions to the needs of the patients and their relatives.

### Statistical analyses

We will use R software [34]. To evaluate the benefit of DULCINEA therapy through the CAL and the BDAE questionnaires, we will use mixed effects linear regression models, a statistical model particularly useful for longitudinal studies with repeated measures. Because of their advantage in dealing with missing values, mixed effects models are usually preferred over other approaches, allowing for an adjustment of the treatment effects by the baseline values and the period effect in crossover trials. Given this study has a crossover design with two treatment sequences (treatment-washout/waitlist-treatment) and two phases (phase 1 and phase 2) with a baseline evaluation of all the patients, we will consider treatment and phase as principal fixed effects, the treatment*phase as interaction effect and the patient nested in the treatment sequence as random effect. For pairwise post hoc comparisons, we will use the Bonferroni test. Analysis will also look for significant differences within test scores and variables scored for each dubbing session.

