**Fig. 1 Fig1:**
[figure not shown]
Study design

A computer-generated random list of numbers provided by an independent statistician will be used for study allocation. The randomization sequence will be created using SAS V.9.4 statistical software (procedure “PROC PLAN”) with a 1:1 allocation. No randomization seed will be specified. The randomization seed will be generated taking the hour of the computer when the program is executed. Randomization will be performed centrally through an Interactive Web Response System in order to conceal the sequence until interventions are assigned (REDCap 8.7.4 - 2021 Vanderbilt University).

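### The listed primary model has no baseline term, although baseline adjustment is a stated reason for using it; this costs precision in the phase 1 between-group contrast

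*Protocol article*

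**What the plan says.** The Statistical analyses section of the protocol article prefers mixed models partly for "allowing for an adjustment of the treatment effects by the baseline values and the period effect in crossover trials". It describes two sequences and two phases, and sets out the model in these words: "with a baseline evaluation of all the patients, we will consider treatment and phase as principal fixed effects, the treatment*phase as interaction effect". Patient nested in sequence is the random effect. The list contains no baseline score, and phase has two levels, neither of which is the baseline visit.

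The baseline data exist. The Intervention section opens with a CAL and BDAE evaluation. The Primary outcomes section schedules both instruments three times per patient, the first time after allocation.

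Two other sections bear on the point. Under Sample size estimates the authors write "we estimated that we would need a sample size of 27 patients in each arm for an 80% power and a 0.050 two-sided significance level", with CAL as the outcome; they give no CAL difference or SD and rely on an earlier trial of a different therapy. The Discussion says it is unknown how long any benefit lasts, and gives finding out whether it lasts at least 3 months as one reason for the crossover design.

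**The concern.** The stated reason for the model and the stated model do not agree. Baseline adjustment is named as a benefit, but no listed term delivers it.

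The random patient effect may seem to do the work instead. It does so only for comparisons within patients. Treatment, phase and their interaction together fit the four sequence-by-phase means exactly, so the phase 1 treatment effect is a comparison of two different sets of patients. Stable differences between patients stay in its error.

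This trial may have to rely on that contrast. If the benefit persists beyond the washout, group 1's phase 2 control scores still carry it. Under full persistence the phase 2 contrast is zero, and the average over phases estimates half the true effect. The phase 1 contrast is randomised and free of carryover, and it is the one left unadjusted.

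The pilot is also meant to inform the sample size of a definitive trial. An unadjusted variance carried forward would make that trial larger than an adjusted analysis needs.

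**Working it through.** **Inputs.** 27 patients per arm, two-sided 0.05 and 80% power come from Sample size estimates. The model terms come from Statistical analyses. The correlation r between two assessments of the same patient is not in the document and is assumed, from 0.3 to 0.8. Also assumed are equal SDs (set to 1), the same r between all pairs of assessments, and complete data.

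**The plan's own figure.** Without a difference or SD, 27 per arm can be neither confirmed nor refuted. Solved backwards for an unadjusted two-group comparison:

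- Normal approximation: d = (1.960 + 0.842) × sqrt(2/27) = 2.802 × 0.272 = 0.762 SD.
- t-test: d = 0.777 SD.

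**Phase 1 contrast as listed.** SE = sqrt(2/27) = 0.272 SD, whatever the value of r.

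**Phase 1 contrast with baseline as covariate.** SE = sqrt(2(1 − r²)/27).

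**Contrast averaged over both phases.** Within each patient this uses the difference between the two phases, so SE = ½ × sqrt(2 × 2(1 − r)/27) = sqrt((1 − r)/27). A baseline covariate shifts both phases of a patient equally and cancels.

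| Assumed r | Phase 1 SE, no baseline | Phase 1 SE, baseline adjusted | Reduction | Phase-averaged SE, with or without baseline |
|---|---|---|---|---|
| 0.3 | 0.272 | 0.260 | 5% | 0.161 |
| 0.5 | 0.272 | 0.236 | 13% | 0.136 |
| 0.7 | 0.272 | 0.194 | 29% | 0.105 |
| 0.8 | 0.272 | 0.163 | 40% | 0.086 |

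**Baseline as a first response row.** Exact generalised least squares with a common baseline mean gives the same phase 1 SE as the covariate at r = 0.5, 0.7 and 0.8: 0.236, 0.194 and 0.163.

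**Simulation check.** In 150 simulated trials at r = 0.7, the phase 1 estimate had an SD of 0.260 without baseline and 0.207 with it. The phase-averaged estimate had 0.109 either way. Both agree with the formulas within simulation error.

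**What this means for power, as illustration only.** At the back-solved 0.762 SD, phase 1 power rises from 80% to 84%, 90%, 97.5% and 99.7% at r = 0.3, 0.5, 0.7 and 0.8. For a later trial sized on the phase 1 contrast, the ratio of unadjusted to adjusted sample size is 1/(1 − r²), which at r = 0.7 is 1/0.51 = 1.96.

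**The case against.** The strongest reply is that the article does not show baseline to be unused. It names baseline adjustment, and it introduces the model by noting that all patients have a baseline evaluation. The abstract also describes the primary outcomes as differences before and after therapy. If change from baseline is the response, the phase 1 SE is 0.272 × sqrt(2(1 − r)), which is 0.211 at r = 0.7 and 0.172 at r = 0.8, close to the adjusted values. At r = 0.5 it is 0.272, so change scores gain nothing there. If baseline is a response row, the adjusted precision is already achieved. A SAP that is not shown may settle this.

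This limits the point but does not remove it. The article does list its terms; a baseline row would need a third phase level, and only two are defined. The listed model departs from its own rationale.

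The reply that the phase-averaged contrast gains nothing is also correct. It protects the plan only if that contrast is primary and carryover is negligible. The article does not name a primary contrast, and the Discussion leaves persistence open.

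Two stronger readings are tempting:

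- **Time since stroke.** A reader might infer that it too is available, strongly prognostic and wrongly omitted, because recruits include patients "discharged from the Speech Therapy Unit at La Paz University Hospital during the year before the start of the study" and members of patients' associations, and no stratification factor is stated. The document does not list time since stroke as a recorded variable and gives no evidence of its prognostic strength. If it explained a further 5% of variance (assumed), the SE ratio at r = 0.7 would move only from 0.714 to 0.678.
- **Chance imbalance.** A reader might infer that it could be as large as the effect sought. A baseline imbalance of 0.777 SD is 0.777/0.272 = 2.9 standard errors, with a two-sided probability of about 0.4%. At r = 0.7 the share passed on to the outcome has SE 0.7 × 0.272 = 0.19, so 0.777 is about 4.1 standard errors. A two-standard-error imbalance (0.54 SD) would shift the contrast by about 0.38 SD, roughly half the back-solved effect.

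**Conclusion.** The point holds for the phase 1 between-group contrast. Fitted as written to post-baseline scores, the listed model leaves its SE at 0.272 SD. Using the baseline already collected would reduce it by 5% at r = 0.3, 13% at 0.5, 29% at 0.7 and 40% at 0.8. The loss is therefore minor at low correlation and material at moderate or high correlation.

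It does not extend to the phase-averaged within-patient contrast, nor to an analysis in which baseline is already a response row. The correlation is assumed, and the 0.76 to 0.78 SD effect is back-solved from the sample size, so the power figures are not properties of this trial. The document does not support a claim that the plan ignores baseline altogether, or that it wrongly omits time since stroke. The change is worth making because it is nearly free and carries out what the section says it values.

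**What to change.** In Statistical analyses, state that the baseline value of the same outcome (CAL for CAL, BDAE for BDAE) enters the primary model in one of two forms:

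- as a fixed covariate, with the two post-baseline assessments as responses; or
- as a first repeated measure with a common mean in both groups, with phase given a baseline level.

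Define baseline as the first assessment after allocation in both groups. Group 2's assessment at the end of the waitlist is its phase 1 outcome and must not serve as its baseline.

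In the same place, name the primary contrast: the phase 1 between-group difference or the average over both phases.

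The cost is one model term, about one degree of freedom, with no new data, visits or patients.

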## Discussion

Nowadays, one of the major challenges in SLT is to find a standardized, rapid, and low-cost therapy due to the increasing prevalence of stroke survivors; it is estimated that approximately 15–42% of these survivors experience post-stroke aphasia [3]. Although it has been clearly shown that SLT is beneficial for post-stroke aphasia in terms of improved functional communication, reading, writing and expressive language compared with no therapy, the current provision of SLT is heterogeneous with disparities related to the therapy regimen, delivery models, and the treatment setting [7].

In this challenging scenario, the development of an innovative therapy aimed at improving recovery from stroke as well as quality of life of stroke survivors and their relatives would represent an important advance in this field and would help to improve citizens’ health and wellbeing. In addition, computer programmes and apps to continue therapy at home, shown to improve speech output and narrative production in non-controlled studies [12, 13], could save precious time and money for society, patients, and relatives.

Using audiovisual content showing lip movements, on which dubbing techniques are based, and encouraging both healthy controls and post-stroke aphasic patients to imitate them is proven to activate a network of cortical areas involved in planning and executing speech production as demonstrated in functional MRI studies [35–37]. Therefore, there is a well-known neurobiological basis to support the effects on brain connectivity that DULCINEA therapy may produce. According to our preliminary results [25], this novel approach also helps to integrate various language requirements (the simultaneous practice of coordination of oral muscles, rhythm, and emotional intonation); to increase sustained attention and motivation, thus reducing dropouts and to improve functional language (as words are practiced within realistic frameworks, namely, the film scene). Compared with other trials on computer-based SLT, the DULCINEA trial allows the patient and their relatives to choose the target words to be dubbed, according to their needs and preferences. However, given that it is a novel therapeutic approach to post-stroke aphasia, it is unknown whether the potential improvement in functional communication is long-lasting or how long the effects last. This was one of the reasons for the choice of a cross-over design, to evaluate whether the effects last at least 3 months after the intervention. We chose this time point because it was a feasible washout period in our prior feasibility trial on aphasia treatment and it is a longer period than in other trials on aphasia, which lasted only 6 weeks [38, 39]. A 3-month period will give us a better approach to establishing the stability of the potential improvements.

Finally, it has been reported that the relevance and translation of research findings may be increased by considering research outcomes which are important to people living with aphasia [40]. In this sense, we incorporated from the very beginning the voice of patients with aphasia and their relatives, who contribute to the study design, mainly in the selection of words to be dubbed, and in the educational and dissemination activities scheduled in the DULCINEA project.

## Conclusions

This pilot clinical trial exemplifies the collaboration between hospitals, universities, and patients in the development of a new therapeutic tool based on dubbing techniques in our aim to improve the recovery and quality of life of aphasic patients based on functional communication, computer-based technology, and standardized test assessment.

## Trial status

Recruitment started in December 2020, and it is planned to end by March 2023. Protocol version 1.0, date 15 July 2019; Protocol version 2.0, dated October 7, 2020).

## Data Availability

Trial results will be published in Open Access journals. Raw data will be available from the corresponding author upon reasonable request.

## Abbreviations

BDAE: Boston Diagnostic Aphasia Examination
CAL: Communicative Activity Log questionnaire
DULCINEA: DUbbing Language-therapy CINEma-based in Aphasia post-Stroke
GHQ-12: General Health Questionnaire
SADQ10: Stroke Aphasic Depression Questionnaire
SAQOL-39: Stroke Aphasia Quality of Life Scale
SLT: Speech and language therapy
WAB-R: Western Aphasia Battery Revised
WP: Work package
